**Table 4. cRCT outcomes**

| **Outcome** | **Outcome type** | **Indicator** | **Source** | **Timing of assessment** | **Statistical Analysis** |
| --- | --- | --- | --- | --- | --- |
| **Aim 1** | | | | | |
| FP discontinuation | Primary | No FP used at exit (among FP users who desire pregnancy prevention) | Survey, clinic records | Quarterly, by 2 years | Cox proportional hazards, time to first event |
| Uptake of dual methods | Secondary | Using condoms and another modern FP method | Survey, clinic records | Quarterly, by 2 years | Poisson GLM (log-link with robust SE |
| Unmet need for FP | Secondary | Desire for pregnancy prevention but not using FP | Survey, clinic records | Quarterly, at 2 years | Poisson GLM (log-link with robust SE) |
| VL suppression at conception | Exploratory/  modeled | VL<1000 copies/mL among women planning pregnancy/pregnant | Lab results | First clinic visit when pregnant/planning pregnancy | Poisson GLM (log-link with robust SE) |
| Unintended pregnancy | Exploratory/  modeled | Pregnancy among women not intending pregnancy (excludes ambivalence) | Survey, clinic records, model | By 2 years | Poisson GEE (log-link with robust SE) |

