## 12.4 Sample Size Determination

| **Table 3. Number of clusters needed assuming n=300 women per cluster (accounting for up to 10% attrition) 80% power, α=0.05, two-sided testing, coefficient of variation=0.2** | | | | | |
| --- | --- | --- | --- | --- | --- |
| *FP discontinuation* ***Arm 1*** | | | | | |
| **Arm 2** | **20%** | **25%** | **30%** | **35%** | **40%** |
| **45%** | 6 | 8 | 12 | 26 | 103 |
| **50%** | 6 | 6 | 10 | 14 | 32 |
| **55%** | 4 | 6 | 8 | 10 | 18 |
| **60%** | 4 | 6 | 6 | 8 | 12 |

Based on literature ([7](#_ENREF_7)) and recent data among women receiving HIV care in Kenya ([63](#_ENREF_63)) we anticipate 50% of women in the control arm will discontinue FP by 2 years. Assuming α=0.05, 2-sided testing, and a coefficient of variation of 0.2, 10 clinics (5 per arm), and 300 women/clinic we have 80% power to detect a 40% reduction in discontinuation for reasons other than planned pregnancy (30% discontinuation rate) (**Table 3**). Prior data suggest the coefficient of variation falls as cluster size increases, is often ≤0.25, but rarely >0.5; therefore, a coefficient of variation of 0.2 is expected to be adequate. We will enroll 347 women to allow for 10% attrition after enrollment plus additional attrition between consenting and the return visit for use of the counseling tool and completion of enrollment, for a total sample size for analysis of 3300 women. Power was conservatively calculated factoring in potential attrition. With 10 clusters we will also have sufficient power to detect a difference in unmet need for FP (reduction from 25% to 15%) and an increase in dual method use from 40% to 65%.

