**12.5 Statistical analysis** We will compare facility and individual characteristics (accounting for clustering) to determine adequacy of randomization. In the primary intent-to-treat analysis, we will compare time to FP discontinuation (no method use for >1 month, 2 years of follow-up) using Cox-proportional hazards regression, accounting for clustering.([87](#_ENREF_87)) Women not initially on FP at baseline will enter the analysis once initiating FP. We will use Poisson generalized linear models (GLMs) with a log-link function to compare secondary outcomes, an offset of time and robust standard errors to compare rates of dual method use and unmet need for FP between arms accounting for clustering (Table 4). This analytical approach is appropriate for rare outcomes.([88](#_ENREF_88), [89](#_ENREF_89)) We will conduct an exploratory analysis comparing VL suppression (<1000 copies/mL) between arms among women who become pregnant using generalized estimating equations with a log link, exchangeable correlation structure, and clustering by clinic. Additional exploratory analysis comparing unintended pregnancy rates between arms will be done using a Poisson GLM as described above. Data will be disaggregated by age, marital status, fertility plans, FP method and user type (initiator, continuer, or switcher). Although we expect low attrition and no differences in attrition by arms we will assess whether there is selection bias due to attrition by comparing women retained vs. not retained and report any differences. We will use multivariate imputation by chained equations to impute variables with >25% missing values.

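### The primary outcome is defined three ways: Section 12.5, the Table 4 indicator and Section 12.4 count different events in different women

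*Protocol*

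**What the plan says.** Three places in the protocol describe the primary outcome.

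- **Section 12.5 (Statistical analysis):** "we will compare time to FP discontinuation (no method use for >1 month, 2 years of follow-up) using Cox-proportional hazards regression". On who is at risk it says "Women not initially on FP at baseline will enter the analysis once initiating FP". It states no restriction by pregnancy intention.
- **Table 4 (cRCT outcomes), primary row:** the indicator is "No FP used at exit (among FP users who desire pregnancy prevention". The timing cell of the row is "Quarterly, by 2 years" and the analysis cell is "Cox proportional hazards, time to first event".
- **Section 12.4 (Sample Size Determination):** "we anticipate 50% of women in the control arm will discontinue FP by 2 years". The target is 30% in the intervention arm, and the event is discontinuation that is not due to a planned pregnancy.

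Nothing in the protocol says which version governs or how they fit together.

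**The concern.** The event and the population both differ, and they differ for the primary outcome.

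The Section 12.5 event is a spell without a method, which can occur at any time and be followed by a restart. The Table 4 indicator is a state at one time point. The Table 4 row also conflicts with itself: a status read once at exit has no first occurrence and no event time for a Cox model to use.

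On population, Table 4 keeps only users who want to prevent pregnancy, Section 12.4 leaves out stops for planned pregnancy, and Section 12.5 as worded does neither.

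The women affected are not a marginal group. The background sections describe an intervention meant to help women switch, restart, or stop in order to conceive, and these are the women whom the definitions classify differently. What is at stake is what the trial estimates and which women count as failures.

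**Working it through.** **1. The plan's own figure.** For 50% against 30%, Table 3 gives 10 clusters. Inputs from Section 12.4: two-sided α = 0.05, 80% power, coefficient of variation k = 0.2, 300 women per cluster with up to 10% attrition. I used the Hayes-Bennett formula for unmatched clusters:

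c per arm = 1 + (1.960 + 0.842)² × V / (p0 − p1)², where V = p0(1−p0)/n + p1(1−p1)/n + k²(p0² + p1²)

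- With n = 270 (300 less 10%, my reading of the attrition note), V = 0.46/270 + 0.04 × 0.34 = 0.01530. Then c = 1 + 7.849 × 0.01530/0.04 = 4.003, rounded up to 5 per arm, or 10 in total. This reproduces Table 3.
- With n = 300, c = 3.97, which would give 8 in total.

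The formula compares two proportions. It works equally for a cumulative risk and for a status at exit, so the sample size does not show which definition was meant.

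**2. How individual women are classified.**

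| Woman | Section 12.5 as worded | Table 4 indicator | Section 12.4 |
| --- | --- | --- | --- |
| Stops for 3 months in year 1, restarts, using FP at exit | Event | Not an event | Not stated whether a restart cancels it |
| Wants to prevent pregnancy, stops two weeks before exit | Not an event (gap too short) | Event | Gap length not stated |
| Stops for a planned pregnancy | Event | Outside the population while she wants to conceive | Not counted |

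For the third row, Study Limitations gives a pregnancy incidence of 10 per 100 person-years. At a constant rate that is 1 − exp(−0.2) = 18% of women over 2 years. The planned share is not given, so this shows only that the group need not be negligible.

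**3. Illustration of the first row.** The documents give no resumption rate, so the rates below are assumptions. Suppose 50% and 30% are 2-year risks of a first discontinuation at constant hazard: λ0 = −ln(0.5)/2 = 0.347 per year and λ1 = −ln(0.7)/2 = 0.178 per year. Suppose stoppers resume at rate μ, equal in both arms. The model treats every stop as a qualifying gap and ignores the one-month threshold. Then:

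proportion not using at 2 years = λ/(λ+μ) × (1 − exp(−2(λ+μ)))

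Median gap = 12 × ln2/μ months. Power = Φ(|p0 − p1|/√(V/(c−1)) − 1.96) with c = 5, n = 300, k = 0.2.

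| μ per year | Median gap | Control | Intervention | Ratio | Power |
| --- | --- | --- | --- | --- | --- |
| 0 | no restart | 50.0% | 30.0% | 0.60 | 0.90 |
| 0.25 | 33 months | 40.5% | 24.0% | 0.59 | 0.90 |
| 0.5 | 17 months | 33.4% | 19.5% | 0.58 | 0.90 |
| 1 | 8 months | 24.0% | 13.7% | 0.57 | 0.90 |
| 2 | 4 months | 14.6% | 8.1% | 0.55 | 0.87 |
| 4 | 2 months | 8.0% | 4.3% | 0.54 | 0.80 |

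In this model the two definitions agree only if nobody resumes. The level falls sharply and the ratio moves little.

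**4. Unequal resumption, also assumed.** With 0.5 per year in control and 1 in the intervention arm, exit status is 33.4% against 13.7% (ratio 0.41). With 1 and 0.5, it is 24.0% against 19.5% (ratio 0.81). With the extreme pair 2 and 0.25, it is 14.6% against 24.0%, a reversed direction, while first-event risk stays at 50% against 30%.

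**The case against.** The strongest reply is that one table cell is out of line and there are not two rival analysis plans. Section 12.5 and the timing and analysis cells of the Table 4 row all point to a time-to-event analysis, no test of an exit proportion is specified for the primary outcome, and a statistical analysis plan not seen here may settle the matter. The first part stands and makes the intended analysis easy to infer. It does not remove the conflict, because the indicator cell is where a reader looks for the definition, and an analysis plan could only resolve it by overriding protocol text. Nor does it touch the population mismatch, in which Section 12.5 is the version without a restriction. Table 4, not Section 12.5, is also the source of the word first, so even the time-to-event version has to be assembled from two places.

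Four stronger readings are tempting, and the documents do not support them.

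- **Primary and secondary outcomes become nearly one variable.** Unmet need is "Desire for pregnancy prevention but not using FP", with no limit to FP users, so it includes women who never started. Section 12.5 analyses it with a time offset. Because the denominators differ, setting 50% to 30% beside 25% to 15% proves nothing. Both are in any case the same 40% relative reduction (20/50 and 10/25).
- **The planning figures fit only the cumulative definition.** The wording suits it best, but the formula in step 1 accepts either.
- **The choice of definition would overturn the result or break the power.** With equal resumption the ratio stays at 0.54 to 0.60 and power at about 0.80 to 0.90. The reversal needs resumption rates for which the documents give no basis.
- **The definition will be picked after seeing data.** There is no masking, and the timeline foresees analysis throughout the trial, so this is possible, but nothing shows it.

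**Conclusion.** The inconsistency is real and should be corrected before analysis, since it concerns the primary outcome. Women who stop for more than a month and restart, women who stop shortly before exit, and women who stop for a planned pregnancy are classified differently depending on which place is followed.

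The size of the effect on the result cannot be computed from the documents. Under the assumptions of constant hazards and equal resumption, the absolute levels change a great deal (control from 50% to 14.6% at a resumption rate of 2 per year) and the risk ratio little (0.60 to 0.55). The number of clusters is hardly affected at resumption rates up to 2 per year. The defect lies in what is estimated and in whom.

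**What to change.** - **Table 4, primary indicator:** replace it with the time-to-event definition, that is, the first spell of more than one month with no FP method, dated from the quarterly survey and clinic records, over 2 years.
- **Sections 12.4 and 12.5 and Table 4:** use one population and one event rule in all three. Keep the exclusion of discontinuation for planned pregnancy. Copying the Section 12.5 wording into Table 4 unchanged would drop it and count those women as failures.
- **Section 12.5:** state how stops for planned pregnancy enter the Cox model, for example censored or treated as a competing event, and when intention is assessed.
- **No FP at exit:** keep it only as a supportive outcome, or drop it.

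The cost is wording in three places. No new data are needed as long as the quarterly survey records the reason for stopping, which the event in Section 12.4 already presupposes.

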Our team has extensively evaluated a **novel 2-way SMS platform (*Mobile WACh*)** **among women receiving MCH services**, that combines automated SMS and 2-way mobile messaging with a health care worker to deliver RH counseling and support in real-time. In 3 trials, Mobile WACh **improved initiation of postpartum contraception**. We propose to adapt Mobile WACh for a **new population** (non-peripartum WLWH), **new environment** (routine HIV care), **and new outcomes for long-term impact** (contraceptive continuation and safe conception). We anticipate this **tailored version of Mobile WACh** will help **provide women with reproductive life planning support to make decisions** and overcome barriers to achieving RH goals. We hypothesize this novel intervention, grounded in behavioral theory, **will reduce contraceptive discontinuation rates and help women safely plan pregnancies**. Counseling and support delivered via SMS directly to women is also expected to reduce the time and number of topics covered during routine counseling, and as a result relieve providers and health care systems of some of the burden to deliver comprehensive RH services and improve quality.

Design

*We will leverage our team’s extensive, interdisciplinary experience on HIV, RH, and mobile health (mHealth) to implement and evaluate the Mobile WACh Empower intervention in a cluster randomized controlled trial (RCT) proceeded by formative workshops with key stakeholders to refine content and approach and post-trial scalability evaluations to ensure potential for real world deployment and scale.*

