**MTCT Model** We will adapt an existing MTCT Markov model (*Meisner/Drake review Int AIDS Soc 2021*)([64](#_ENREF_64)), including upstream elements related to pregnancy risk and intentions, and economic impact of Mobile WACh Empower (including intervention costs incurred/averted). Current model parameters include time since HIV diagnosis, ART use/adherence, infant ARV use, viral suppression, and breastfeeding. We will estimate costs of ART provision and other healthcare expenses from the literature. We will adapt our model to incorporate estimates of unintended pregnancies following prior methods*(*[*95*](#_ENREF_95)*)*, including: unmet need for FP among WLWH (from Mobile WACh Empower trial), current maternal ART and infant ARV regimens, and contraceptive failure rates from developing countries. ([96](#_ENREF_96)) Reduction in births among WLWH who desire pregnancy prevention (need for FP) will be calculated based on the ratio of the contraceptive index (1-1.08x contraceptive prevalence rate [CPR] x efficacy) for women who receive the intervention vs SOC (current CPR and unmet need).([95](#_ENREF_95)) We will calibrate the model to estimates of unintended pregnancy reported by Track 20 and MTCT rates in Kenya. We will project intervention impact on unintended pregnancies and MTCT, calculating incremental cost-effectiveness ratios (ICERs) as the ratio of costs divided by the difference in health outcomes (unintended pregnancy and infant HIV) of the intervention compared to the SOC over a 20 year time horizon. Consistent with guidelines, we will discount costs and health benefits at 3% annually; ICERs below Kenya’s per capita gross domestic product will be considered cost-effective([97](#_ENREF_97)). We will conduct sensitivity analyses to identify influential assumptions.

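### The viral suppression outcome is defined on two different populations and an unclear time point, and its between-arm contrast is open to selection bias if read as an effect on viral load

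*Protocol*

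**What the plan says.** Section 12.5 plans an exploratory analysis "comparing VL suppression (<1000 copies/mL) between arms among women who become pregnant". The method is "generalized estimating equations with a log link, exchangeable correlation structure, and clustering by clinic". The section gives no time point for the VL.

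The Table 4 row opens "VL suppression at conception | Exploratory", and its outcome type also carries the label modeled. Its indicator is "VL<1000 copies/mL among women planning pregnancy/pregnant", its timing is "First clinic visit when pregnant/planning pregnancy", and its analysis is a Poisson GLM with log link and robust standard errors.

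The summary states the hypothesis that the intervention "will reduce contraceptive discontinuation rates and help women safely plan pregnancies".

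For Aim 3, section 11.2 says that Aim 1 outcome data will be combined with costs in a mathematical model. The model paragraph says "Current model parameters include time since HIV diagnosis, ART use/adherence, infant ARV use, viral suppression, and breastfeeding". It does not say where the suppression value will come from. The only clinical input that this paragraph names as coming from the trial is unmet need for family planning.

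**The concern.** There are two problems.

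First, an analyst cannot tell from the protocol who is in the denominator or when VL is taken. A woman who plans a pregnancy but never conceives counts in Table 4 and not in section 12.5. For a woman who plans and then conceives, the Table 4 value can predate conception. For a woman who does not plan, it follows conception.

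Second, becoming pregnant and planning a pregnancy are both events after randomisation, and the intervention is designed to change them. Randomisation makes the arms comparable over all enrolled women. It does not make the pregnant or planning women in one arm comparable with those in the other. If the intervention prevents unintended pregnancies, and suppression is lower in those pregnancies, suppression among pregnant women rises with no change in any woman's VL. Under the Table 4 definition, more planning in the intervention arm would also move more of that arm's measurements to before conception.

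At stake is how an exploratory result is read and, if the figure is used there, what enters the Aim 3 model.

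**Working it through.** **The definitions side by side**

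| | Section 12.5 | Table 4 |
|---|---|---|
| Population | Women who become pregnant | Women planning pregnancy or pregnant |
| VL time point | Not given | First visit when pregnant or planning; the title refers to conception |
| Model | Log-link GEE, exchangeable, clustered by clinic | Log-link Poisson GLM, robust SE |

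**Size of the pregnant group.** The protocol gives no sample size or power for this outcome, so there is no stated figure to reproduce. The limitations section gives a pregnancy incidence of 10 per 100 person-years. With 10 clinics of 300 women followed for 2 years, 3000 × 2 × 0.10 = 600 pregnancies. With the 3300 women that section 12.4 also gives, the figure is 660. Adding women who are planning a pregnancy changes this denominator by an amount the protocol does not give.

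**Shift from mix alone.** None of the following inputs is in the protocol; all are assumptions, and the true effect on VL is set to zero.
- f, unintended share of control-arm pregnancies: 30% to 50%
- s_p, suppression in planned pregnancies: 92% to 95%
- s_u, suppression in unintended pregnancies: 80% to 88%
- r, relative cut in unintended pregnancies: 20% to 40%

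Control: S0 = f·s_u + (1 − f)·s_p

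Intervention: S1 = [f(1 − r)·s_u + (1 − f)·s_p] / [f(1 − r) + (1 − f)]

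Worked case with f = 0.5, s_p = 0.95, s_u = 0.80, r = 0.4: S0 = 0.400 + 0.475 = 0.875. S1 = (0.3 × 0.80 + 0.5 × 0.95)/0.8 = 0.715/0.8 = 0.894.

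| f | s_p / s_u | r | S0 | S1 | Difference (points) | Ratio of unsuppressed shares |
|---|---|---|---|---|---|---|
| 0.3 | 92% / 88% | 20% | 90.8% | 91.0% | 0.18 | 0.981 |
| 0.3 | 95% / 85% | 20% | 92.0% | 92.5% | 0.45 | 0.944 |
| 0.5 | 95% / 85% | 40% | 90.0% | 91.3% | 1.25 | 0.875 |
| 0.4 | 95% / 80% | 40% | 89.0% | 90.7% | 1.71 | 0.844 |
| 0.5 | 95% / 80% | 40% | 87.5% | 89.4% | 1.88 | 0.850 |
| 0.5 | 90% / 90% | 40% | 90.0% | 90.0% | 0 | 1.000 |

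The range is 0.2 to 1.9 points where suppression differs by intention, and zero where it does not. If planned pregnancies also rise by 20%, the range becomes 0.3 to 2.5 points.

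**What happens in a model.** Take 100 control pregnancies with f = 0.5, s_p = 0.95, s_u = 0.85, r = 0.4.
- Control: 50 × 0.05 + 50 × 0.15 = 2.5 + 7.5 = 10 unsuppressed.
- Intervention: 50 × 0.05 + 30 × 0.15 = 2.5 + 4.5 = 7 unsuppressed among 80, a share of 8.75%.
- Arm-specific pregnancies times arm-specific share: 80 × 0.0875 = 7, which is correct.
- If the averted unintended pregnancies have already been removed at their own suppression level (leaving 7), and the arm ratio 0.0875/0.10 = 0.875 is then applied as a VL effect, the result is 7 × 0.875 = 6.1. That is a fall of 39% when the true fall is 30%.

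**The case against.** **A reader might infer that the contrast is biased.** The protocol does not show that. Bias arises only if the intervention changes the mix of pregnancies and suppression differs across that mix, and the protocol gives no figure for either. Neither direction nor size can be derived from it.

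**A reader might infer that this contrast feeds the MTCT model.** The modeled label and the general Aim 3 sentence make use of trial VL data plausible. However, viral suppression is listed as a parameter of an existing model, and the reduction in births is computed from a contraceptive index. No sentence says that the between-arm VL contrast is used.

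**A reader might infer that the change in mix is bound to be counted twice.** It is not. The change in mix is part of the true total effect on unsuppressed conceptions, and the calculation above shows that arm-specific suppression with arm-specific pregnancies gives the right count. Double counting needs the further step of applying the arm ratio as a VL effect on top of averted unintended births.

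**The shift is small against the noise.** With about 300 pregnancies per arm and an assumed 90% suppression, the 95% half-width for the difference is 1.96 × √(2 × 0.9 × 0.1/300) = 4.8 points before any clustering. This stands, and it limits the weight of the point. It does not settle which women are analysed.

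**Section 12.5 disaggregates data by fertility plans.** This is helpful description. Within each stratum, though, the women compared are still selected by an event after randomisation.

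**The GEE and Poisson GLM labels are close relatives.** This stands. The protocol uses the labels loosely, and the unintended pregnancy outcome has the reverse mismatch. The difference in model is mostly labelling; the differences in population and timing are not.

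**A comparison over all women mixes conception with suppression.** This also stands. If the intervention supports more wanted pregnancies, unsuppressed conceptions could rise while suppression improves. The comparison therefore has to be read with the pregnancy rates by intention.

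**Conclusion.** The concern holds in a limited form. One outcome has two populations, and its measurement time can fall before or after conception; this is plain from the text and rests on no assumption. Because both populations are defined by a state the intervention targets, the contrast is open to selection bias if interpreted as an effect on VL. The size, 0.2 to 1.9 points or zero, is an illustration on assumed inputs and not an estimate for this trial. How the VL result will be used in Aim 3 is left unstated, so the protocol neither commits nor rules out the misuse shown above. The outcome is exploratory, and the primary and secondary conclusions do not depend on it. The change is still worth making because it is cheap and removes an ambiguity from a result labelled as modeled.

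**What to change.** 1. In section 12.5 and Table 4, give one population, one VL time point and one model, and make the row title match the time point.
2. Label suppression among pregnant women as descriptive, and say that it will not be interpreted as an effect on VL.
3. Add a comparison over all enrolled women: conceptions with VL ≥1000 copies/mL per 100 woman-years, by arm, with a Poisson model that accounts for clustering by clinic. Report it beside the pregnancy rates by intention, because it combines conception with suppression.
4. In Aim 3, state which VL figure the model uses. Arm-specific suppression may be paired with arm-specific total pregnancies. The pregnant-only arm ratio should not be applied as a VL effect on top of averted unintended births.

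The cost is wording in section 12.5, Table 4 and the model description, plus one further analysis. The downside is precision: if 10% of about 600 pregnancies were unsuppressed (an assumption), there would be 0.10 × 600 = 60 events across 10 clinics, so the intervals would be wide. That is acceptable for an exploratory outcome.
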